The second study which was a randomised controlled trial, was carried-out to evaluate the effect of a low-literacy immunisation promotion educational intervention in improving DPT/Hepatitis B vaccine uptakes among 366 mother-infant pairs with infants aged ≤6 weeks of age in Karachi, Pakistan. At four months after enrolment, among 179 mother-infant pairs in the intervention group, 129 (72.1%) had received all the 3 doses of DPT/Hepatitis B vaccine while in the control group only 92/178 (51.7%) received all the 3 doses. This finding was statistically significant (ARR = 1.39; 95% CI: 1.06–1.81) [54]. However, none of the studies was guided by any health theory in providing a strategy and a step-by-step summary of specific factors to be considered when developing, implementing, and assessing the health education interventions. Notwithstanding the usual health education given to pregnant women attending antenatal at FMC Gusau, child immunisation uptake is still low. It is important therefore, to compare the results of our intervention group and that of control group to help in evaluating the effectiveness of the intervention.

Therefore, there is a need to develop and implement a theory-based intervention with application of social cognitive theory to evaluate the effectiveness of immunisation health education in improving the knowledge, attitude, outcome expectation, self-efficacy; cultural beliefs and assumptions on religious regulations of antenatal mothers which will hopefully increase childhood immunisation uptake and decrease mortality and morbidity among children in Nigeria. The intervention module that will be developed from this study may be adopted and consolidated into the routine health education delivering to pregnant women at the time of their antenatal care visits. This will provide better knowledge to antenatal mothers concerning the importance of child immunisation. The study findings could benefit policy makers in making decisions and formulating appropriate guidelines and policies with regards to childhood immunisation uptake in order to reduce childhood mortality and morbidity of VPDs. Other researchers may also adopt the validated questionnaire and intervention modules that will be developed from this research for future studies.

The research questions of this study are as follows:

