### Intervention

The participants in the intervention group will receive the ‘‘Immunisation Health Education Intervention” while the participants in the control group will receive ‘‘usual care”. The proposed interventions will be implemented at 35 gestational weeks after the baseline data has been collected from the participants. Based on the recommendation of McMillan [59], educational interventions should be carried out using approaches that are in accordance with what is used in practice. It is based on this, that the delivery of educational interventions in this study will be done at group levels in a two session. Every session will be composed of forty participants, while the facilitator of each of the sessions will be a midwife nurse.

The process of module delivery will be closely monitored and supervised by the investigator, and the relevant feed-back will be given to the facilitator in order to ensure that the module is followed accordingly. The five modules will be delivered by the facilitator, who will ensure that the participants are actively engaged. It is estimated that the delivery sessions will last for 30 minutes, 30 minutes, 30 minutes, 1 hour, 30 minutes, 45 minutes, 1 hour and 30 minutes. For modules 1, 2, 3, 4 and 5 respectively *(Refer to S2 File)*. The participants will be allowed to take short breaks of about 10 to 15 minutes between modules. Each participant will be given the chance to demonstrate what she has learnt, and corrective feed-back will be provided at the end of the modules. A compensation fees of (500 Naira) approximately 1.2 USD will be given to the participants in the intervention group in favour of their transportation. The mothers in the intervention group will also be receiving a mobile call reminder at 7 days and 1 day before their childhood immunisation schedule. The participants in the control group will not receive any mobile call reminder. Any mother in either the intervention or control group who completed her child vaccination from 0-doses to penta-3 will receive a baby pampers at the end of the intervention which will cost N700 (Naira) approximately 1.5 USD as recommended by Bandura’s [60].

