#### Structure of the immunisation health educational intervention modules

The intervention will be comprised of five modules, designed to cover each of the constructs of the SCT as presented in S2 File. The knowledge construct will be covered by the first and second modules, the third module will cover the attitude construct, the fourth module will cover the outcome expectation construct, while the fifth module will cover the construct for self-efficacy *(Refer to S2 File).*

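### Only the intervention arm gets reminder calls before immunisation, so a difference in uptake measures education plus calls and cannot be credited to the education alone

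*Protocol article*

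**What the plan says.** **What the arms receive (Intervention section).** The intervention arm gets the education sessions, and then: "The mothers in the intervention group will also be receiving a mobile call reminder at 7 days and 1 day before their childhood immunisation" schedule. For controls the text is explicit: "The participants in the control group will not receive any mobile call reminder". A payment is also described for one arm only: "A compensation fees of (500 Naira) approximately 1.2 USD will be given to the participants in the intervention group in favour of their transportation". A gift for completing the vaccine series is offered equally: "Any mother in either the intervention or control group who completed her child vaccination from 0-doses to penta-3 will receive a baby pampers". Usual care is a set of general antenatal lectures that already includes immunisation.

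**What the trial says it evaluates.** The abstract describes the intervention arm as five education sessions guided by the theory-based module. The second research question, the Trial aims and objectives section and the Study design section all speak of a health educational intervention based on Social Cognitive Theory. The section on module structure says: "The intervention will be comprised of five modules, designed to cover each of the constructs of the SCT". None of these places mentions reminder calls or a transport payment.

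**How the result may be used.** The Background says: "The intervention module that will be developed from this study may be adopted and consolidated into the routine health education" given at antenatal visits.

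**Outcomes.** The primary outcome is childhood immunisation uptake. Knowledge, attitude, outcome expectation, self-efficacy, cultural belief and religious-assumption scores are secondary, taken at 6, 10 and 14 weeks after delivery.

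**The concern.** The arms differ in more than the factor named in the aim. A phone call one day before a vaccination date acts on attendance directly, and attendance is what produces uptake. The teaching is given once, at 35 gestational weeks, well before the 6-, 10- and 14-week vaccinations. The calls therefore lie closer to the primary outcome in both time and mechanism.

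What is at stake is what a positive result may be taken to mean. If uptake is higher in the intervention arm, the article as worded would report that health education raised it. A hospital that added the modules to its antenatal lectures without the calls would be relying on an effect that the trial had not estimated.

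**Working it through.** **1. Setting the sections side by side.**

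| Component | Intervention arm | Control arm | Named in abstract, aim, research questions or design? |
|---|---|---|---|
| Five education modules | yes | no | yes |
| Reminder calls, 7 days and 1 day before | yes | no (stated) | no |
| 500 Naira for transport | yes | not mentioned | no |
| Completion gift | yes | yes | no |
| Usual antenatal lectures | not stated | yes | yes, as comparator |

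The modules, the calls and the payment separate the arms. The gift does not.

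**2. What the planned model can identify.** Let A = 1 for the intervention arm and 0 for control, E = receives education, R = receives calls. By design E = A and R = A. A mixed model for uptake with separate effects would be

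logit(p) = b0 + bE·E + bR·R + covariates = b0 + (bE + bR)·A + covariates.

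Only the sum bE + bR can be estimated (any effect of the payment is in the same sum). Adjusting for the 14 covariates listed in the abstract does not change this, and neither does a larger sample. No reminder-only arm or component analysis is described.

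**3. Timing.** Assuming delivery at 40 weeks, the gap from teaching at 35 weeks to the vaccination visits is (40 − 35) + 6 = 11 weeks up to (40 − 35) + 14 = 19 weeks. The calls come 7 days and 1 day before.

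**4. The plan's own figure.** The Sample size determination section gives 196 per group. Its inputs are in a supplementary file that is not shown, so it cannot be formally reproduced. With the third-dose DPT rates of the cited Sokoto trial (33% against 20%), two-sided 5% significance and 80% power (all assumptions here):

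n = [1.96·√(2·0.265·0.735) + 0.8416·√(0.33·0.67 + 0.20·0.80)]² / 0.13² = 179.7, so 180; with continuity correction, 195.

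That makes 196 plausible but not confirmed. The point does not depend on it.

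**5. Illustration with assumed effects.** Suppose education has no effect on uptake and the other components alone raise it by d points. The chance of a significant two-sided result is

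Φ{[d − 1.96·√(2·p̄(1−p̄)/n)] / √[(p1(1−p1) + p0(1−p0))/n]}.

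For p0 = 0.20, p1 = 0.30, n = 196: (0.10 − 1.96 × 0.04374) / 0.04345 = 0.328, giving 0.63.

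| Control uptake | +5 points | +10 | +13 | +15 |
|---|---|---|---|---|
| 10.8% (Zamfara DPT3) | 31% | 78% | 93% | 97% |
| 20% (cited trial, control) | 22% | 63% | 83% | 92% |

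The Study process section reports 382 women randomised equally, so 191 per arm. At 191 the 63% becomes 62% and the 83% becomes 82%. These figures say nothing about how well calls work. They show that, if the calls do work, the trial would readily produce a result that its present wording credits to education.

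**The case against.** The strongest reply is that package trials are legitimate. The calls and the payment are disclosed under the heading Intervention, randomisation protects the comparison, and the estimate of the whole package against usual care is unbiased. All of that stands. It does not remove the mismatch, because the abstract, aim, research questions and design describe education and not a package.

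A second reply is that reminders may belong to the theory. The Discussion says the theory covers environmental as well as personal factors, and the supplementary module file is not shown. That is possible, but in the Intervention section only the completion gift is tied to the theory's source, and the calls are introduced as something the mothers also receive.

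Several stronger readings are tempting but not supported:

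- *The transport money is a rival cause of uptake.* It is called compensation and follows directly on the account of the teaching sessions. It may cover travel to those sessions only; the text does not say.
- *The completion gift confounds the comparison.* It is the same in both arms and cannot account for an imbalance between them.
- *The trial plans to conclude that the modules alone work.* The Background sentence says only that the module may be adopted.
- *The exposure or the calls' share can be given as a number.* The document states neither how many calls each mother gets nor anything that would divide the effect. If no call precedes the birth doses, which the hand card also records, a difference in those doses would not come from the calls.

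**Conclusion.** The point holds as one of attribution, not of validity. The comparison of uptake estimates education plus reminder calls (plus a payment of unclear purpose) against usual care, and no planned analysis can isolate the education. The calls alone are enough to establish this; neither the payment nor the gift is needed.

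The size of the misattribution cannot be derived from the document. The power figures above are conditional on assumed control rates and assumed effects of the other components. The conclusion itself rests on two things: the explicit statement that controls receive no calls, and the reading that the calls precede the child's vaccination dates.

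A reader might infer that the trial is biased or cannot inform practice. The documents do not support that: a positive result would be sound evidence for the package. It would not show that modules without calls raise uptake.

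**What to change.** 1. In the abstract, aim, research questions and objectives, restate the contrast as education modules plus reminder calls (and transport payment) against usual care. State what the transport payment is for.
2. Limit the conclusion on uptake to that package.
3. Qualify the Background sentence on adopting the module, so that it does not rest on the uptake result for modules delivered without calls.
4. Interpret the construct scores already planned as secondary outcomes (knowledge, attitude, outcome expectation, self-efficacy and the two belief scores) as the outcomes less directly exposed to the calls. They need no new data, but they are not wholly free of the calls and do not substitute for the primary outcome.

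An education-only conclusion on uptake would have needed the same calls in both arms. That is hardly open now, because the Study process section reports randomisation as done.

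The cost is wording, with notice to the registry and the ethics committee as the Protocol amendments section provides. No change to sample size, data collection or analysis is needed. The downside is a narrower claim for the modules.

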### Outcomes

The primary outcome for the proposed study is childhood immunisation uptake and the secondary outcomes are: improved knowledge scores, improved attitude scores, improved outcomes expectation scores, improved self-efficacy scores, improved cultural beliefs scores and improved assumptions of religious regulations scores. They will be taken at 6 weeks post-delivery, 10 weeks post-delivery and 14 weeks post-delivery *(Refer to S3 File).*

### Participants timeline

The recruitment time will be seven weeks and the study participants will be recruited at their 24 to 33 weeks period of amenorrhea. After completing the intervention, the study participants will be followed-up at three times points (6-weeks post-delivery, 10-weeks post-delivery and 14-weeks post-delivery). The expected duration of participation in the study is 22 weeks approximately 6 months.

### Ethics approval and consent to participate

Ethical approval for the proposed study was received from both the Jawatankuasa Etika Universiti Putra Malaysia (JKEUPM) (reference number: JKEUPM-2020-398) and Federal Medical Centre Gusau, Zamfara State (reference number: FMC/2019/985/23). A respondent’s information sheet in Hausa language will be provided by a nurse from antenatal care unit to each participant, from whom informed consent will be obtained. The study has been registered with the “Pan African Clinical Trials Registry” with unique identification number for the registry PACTR202006722055635. The participants information that will be provided and their identity will remain confidential and solely for the purpose of this research. Participation in the study will be voluntary and any of the study participants also has the authority to withdraw at any point of the intervention *(Refer to S4 File)*.

### Study process

An illustration of the study process was done in accordance with CONSORT statement [55]. During the eight weeks recruitment period, a total of 551 pregnant women had been assessed for possible inclusion in the study out of which 159 did not meet the inclusion criteria while ten declined to participate. The remaining three hundred and eighty-two participants were then randomly assigned equally, to either the intervention or the control group. SPIRIT schedule of the study and flow diagram of the study are shown in Figs 1 and 2 respectively. The baseline data of the study participants has been taken and they will both be followed up at 6 weeks post-delivery, 10 weeks post-delivery and 14 weeks post-delivery to assess the effect of the intervention regarding their knowledge, attitude, outcome expectations, self-efficacy, cultural beliefs and assumptions of religious regulations towards child immunization, as well as to assess their child immunization uptake.

**Fig 1 pone.0263436.g001:**
[figure not shown]
SPIRIT schedule of enrolment.

**Fig 2 pone.0263436.g002:**
[figure not shown]
Consort study flow chart of the intervention and control groups.

### Study instrument

The instruments that will be used in this proposed study includes the immunisation health educational intervention modules and the data collection tools; which will comprise of a questionnaire and the study pro forma will also be used.

### The immunisation health education intervention modules

#### Development of the immunisation health education intervention modules

The sources of information that will be used in developing the modules include:

Basic Guidelines for Routine Immunisation Service Provider (Nigeria Federal Ministry of Health).World Health Organization publications on immunisation.Publications from studies conducted in Nigeria on childhood immunisation.

The modules were developed based on the constructs of social cognitive theory.

#### Structure of the immunisation health educational intervention modules

The intervention will be comprised of five modules, designed to cover each of the constructs of the SCT as presented in S2 File. The knowledge construct will be covered by the first and second modules, the third module will cover the attitude construct, the fourth module will cover the outcome expectation construct, while the fifth module will cover the construct for self-efficacy *(Refer to S2 File).*

#### Training of the module facilitator

The modules will be delivered by a midwife, who will also serve as a facilitator at all the health education sessions during antenatal visits. The researcher shall deliver a one-time one-on-one training session to the facilitator. The training session, which will involve teaching the midwife how to deliver the contents to the respondents, will last for about 4 hours. Before the midwives start delivering the modules, another session will be held to revise what they were taught in the previous session, so as to ensure that they are properly equipped to deliver the modules.

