### Eligibility criteria

The eligibility criteria for inclusion into the study will be as follows:

Antenatal mothers of age 18 years and above who are in third trimesters (28–35 gestational weeks); mothers with single pregnancy; must be mothers who planned to deliver and intended to attend the clinic to immunise their children at Federal Medical Centre Gusau; citizens of Nigeria and those resident in Gusau.

The following will be excluded from the study:

Mothers without good understanding of Hausa language as the intervention will be delivered in Hausa language; mothers who attended previous health education intervention on immunization will be excluded to minimise confounding; mothers living in the same household to minimise contamination; mothers of family with nomadic lifestyle will also be excluded as previous study revealed low immunisation uptake among children whose mothers’ practice nomadic lifestyle [20].

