### Implementation

Two staff of the antenatal care unit will assist in assigning groups to the participants independently. The first staff will hand over the sealed envelopes to the participants in a serial order, and afterwards, the staff will be asked to match the serial numbers on the allocation envelopes with the participants’ given serial numbers succeeding the random sampling. Subsequently, the participants will be directed to the second staff, who will then open the envelopes and inform them of the date to come for their health education session based on the group they fall under. After this is done, the group to which the participant belong to, will be documented on a sheet provided. All the study participants will be given a hand card, which is the study pro forma containing the child’s serial number and bio-data. Also, the hand card will contain a short note that shows they have been enrolled into a follow-up study, and seeking any of the attending medical staff (nurse) to kindly assist in completing the post-natal findings as indicated on the card.

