The usual care (standard care) given to antenatal mothers attending FMC Gusau will comprised of general lectures regarding birth preparedness, danger signs in pregnancy, malaria complications, preventions and treatments, breast feeding, postnatal check-up, immunisations, family planning and interactive sessions. These general lectures are always given to antenatal mothers during every visit which last for about two hours.

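### Read literally, the module-trained midwife also facilitates the control arm's antenatal education; the sections are ambiguous and should be reconciled, because module content may reach controls

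*Protocol article*

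**What the plan says.** All places are in the Protocol article.

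- **Training of the module facilitator:** the person giving the modules is described as a midwife with a further role, "who will also serve as a facilitator at all the health education sessions during antenatal visits". The same paragraph starts with one midwife and later refers to midwives in the plural.
- **Intervention (study arms):** the modules go to the intervention group in group sessions of forty, "while the facilitator of each of the sessions will be a midwife nurse". On timing: "The proposed interventions will be implemented at 35 gestational weeks after the baseline data has been collected from the participants". Intervention women receive transport money and call reminders; controls receive no reminders. For the comparator: "while the participants in the control group will receive ‘‘usual care".
- **Intervention (usual care):** the lectures cover a list of antenatal topics that includes immunisation, and interactive sessions are part of them. "These general lectures are always given to antenatal mothers during every visit which last for about two hours". No lecturer is named.
- **Background:** the care already given at the hospital's antenatal clinic is described as health education.
- **Implementation:** after opening the envelope, staff "inform them of the date to come for their health education session based on the group they fall under".
- **Eligibility criteria:** the one exclusion expressly tied to contamination is "mothers living in the same household to minimise contamination".

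**The concern.** Randomisation is by individual woman within one hospital, and usual care already contains teaching on immunisation. The contrast between arms therefore depends on keeping the module content out of that teaching. If the midwife trained to deliver the modules also facilitates the lectures, some of the content may enter them. Control knowledge, attitude, outcome expectation, self-efficacy, cultural belief and religious-regulation scores would then move toward those of the intervention arm, and control uptake might follow. The bias is toward no effect, the comparator would no longer be purely usual care, and no analysis of the trial data could recover the contrast lost.

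**Working it through.** **Step 1. Set the sections side by side.** The plan gives no figure on this point, so the first check is of wording.

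| Question | Literal reading | Narrower reading |
|---|---|---|
| Which sessions does the facilitator clause cover? | All antenatal health education. The clause adds a further role, sets no limit by arm, and places the sessions at antenatal visits, where usual care is given. | Only the intervention's sessions. The section concerns the module facilitator, and the abstract uses the same term for the intervention's five sessions. |
| Is usual care health education? | Yes: Background describes it so, and Implementation speaks of a health education session for whichever group a woman is in. | The Intervention section calls usual care lectures and names a facilitator only for the module sessions. |
| Are controls exposed? | They may be, through a shared facilitator. | Largely not, if the group-based dates keep the arms apart. |

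Neither reading is excluded by the text.

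**Step 2. What separates the arms?** The household exclusion does, and so do the group-based dates and the restriction of the modules to the intervention group. None of these addresses who gives the control lectures. The investigator's supervision is described for module delivery, not for lecture content.

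**Step 3. Illustrate the dilution.** Inputs:

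- n = 191 per arm: 382 randomised equally (Study process), 382 / 2 = 191.
- Significance level 0.05 (Data analyses), taken as two-sided, an assumption.
- Rates from the two earlier trials cited in Background: 33% versus 20% (Sokoto, DPT3) and 72.1% versus 51.7% (Karachi, three doses). The article does not state them as this trial's design inputs.
- c, the fraction of the whole effect that reaches controls: assumed, since the documents give none.
- No losses to follow-up.

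The planned 196 per arm cannot be strictly reproduced, because its inputs are in S1 File, which is not shown. With 20% versus 33%, two-sided 5% and 80% power, the two-proportion formula gives 180, or 195 with continuity correction. One-sided 5% with 90% power gives 196. More than one set of inputs fits, so the design rates are not identified.

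Formulas, with p0 the control rate and p1 the intervention rate:

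- diluted control rate: pc = p0 + c(p1 − p0)
- difference: d = p1 − pc = (1 − c)(p1 − p0)
- with m = (pc + p1)/2: SE0 = √[2m(1 − m)/n] and SE1 = √[(pc(1 − pc) + p1(1 − p1))/n]
- power = Φ[(d − 1.96·SE0)/SE1]

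Worked case, 20% versus 33%, c = 0.2: pc = 0.20 + 0.2 × 0.13 = 0.226; d = 0.104; m = 0.278; SE0 = 0.0458; SE1 = 0.0455; (0.104 − 1.96 × 0.0458)/0.0455 ≈ 0.31; power ≈ 62%.

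| c (assumed) | 33% vs 20%: difference | Power | 72.1% vs 51.7%: difference | Power |
|---|---|---|---|---|
| 0 | 13.0 points | 82% | 20.4 points | 99% |
| 0.1 | 11.7 | 73% | 18.4 | 96% |
| 0.2 | 10.4 | 62% | 16.3 | 92% |
| 0.3 | 9.1 | 50% | 14.3 | 84% |

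**Step 4. Limit of the illustration.** The model dilutes the whole effect. Call reminders at 7 days and 1 day before each vaccination go only to the intervention arm and cannot leak through a lecture. For uptake, c can therefore apply only to the part of the effect that comes from education. The six scores measure what the modules teach and are the more directly exposed outcomes.

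**The case against.** The strongest case on the other side is that the facilitator clause is loose wording rather than a plan to share staff. The abstract applies the term to the intervention's own sessions, the Intervention section names a midwife as facilitator for those sessions only, and the article never says who gives the usual-care lectures. This stands as far as it goes: the narrower reading is a fair one. It does not settle the matter, because that reading leaves the added role in the clause with little meaning and Background describes usual care as health education too.

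A reader might infer that controls are exposed whichever reading is right, because both arms attend the same clinic. The documents do not support that. Sharing a clinic is not sharing a session, and group-based dates, group sessions for the intervention arm and delivery at 35 gestational weeks all point to separate sessions.

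A reader might also infer that the household exclusion is the only protection. It is the only measure labelled as such, but the group-based dates separate the arms as well.

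The remaining objections also stand. The leak fractions have no source in the documents, the rates come from other trials, and it is plausible but not documented that a trained midwife would carry module content into general lectures.

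**Conclusion.** The point holds as an ambiguity with a real consequence on one of its two readings. It is not a demonstrated leak, and it is more than an omitted detail: the article itself assigns the module-trained midwife to sessions described broadly enough to include the control lectures. On the literal reading, bias toward no effect is a risk for uptake and a greater one for the six scores. On the narrower reading the risk is largely avoided.

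The size is unknown. The fall in power from about 82% to 62% rests on an assumed 20% leak of the whole effect, rates borrowed from the Sokoto trial, 191 per arm, a two-sided 5% test and no losses. With the Karachi rates the same leak takes power only from 99% to 92%. Because the reminders cannot leak through lectures, any dilution of uptake would be partial. The change is worth making because it is cheap and the lost contrast cannot be restored in analysis.

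**What to change.** Reconcile Implementation, both parts of Intervention (study arms and usual care) and Training of the module facilitator, so that one statement governs who facilitates which sessions and when. Reword the facilitator clause along these lines:

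> The module-trained midwife facilitates only the intervention-arm module sessions, held on the group-specific dates given at allocation. While control women are still attending, the usual-care lectures are given by existing antenatal staff who have not been trained in the modules.

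State also whether there is one module facilitator or several.

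Study process reports recruitment and baseline as done. If the sessions have already been delivered, record who gave the control lectures during that period and report it as a possible source of dilution when interpreting a small or null difference.

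The cost is a short rewording and a roster arrangement, with less flexibility among existing staff. It assumes that antenatal staff without module training are available, which the article does not state. No added participants or procedures are needed, and the content of usual care does not change.
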